#### **Control arm versus Intervention arm: poor responders (mrTRG3-5)**

- Acute toxicity will be recorded to CTCAE v4.0 protocol. The grade 3- 5 outcomes will be compared between the control and intervention arms on an intention to treat basis.

The preliminary biomarker analysis using proliferative and apoptotic molecular and genomic markers will be hypothesis generating work with descriptive analysis only.

A detailed statistical analysis plan including methods and timing for all endpoints will be written and agreed before commencing any analysis.

Additional endpoints are planned for the phase III trial, including but not limited to quality of life, overall and progression free survival, and data for these endpoints will be collected from patients in the feasibility trial so that they can be included in a pooled analysis of data from the feasibility and phase III trials. Plans for this pooled analysis will be described in full in the proposed phase III protocol. If the planned phase III trial does not commence due to poor recruitment in the feasibility phase, an amendment to this protocol shall be submitted detailing the proposed analysis of this additional data as a part of the feasibility trial.

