## **4.2 SECONDARY OBJECTIVES OF THE FEASIBILITY TRIAL**

### **1. Assess response rate by comparing the reported mrTRG in the control and intervention arm**

Trial participants are randomised with stratification for the key factors that effect response (tumour height, mrEMVI and chemotherapy). Therefore the mrTRG should be similar in the control and intervention arm. In order to avoid the MDT being informed of the mrTRG in the control arm we will report the mrTRG grade in the control arm by centralised assessment. Comparison between the mrTRG in the control versus intervention arm will allow us to evaluate the amount of additional response achieved by using 'upfront' systemic chemotherapy.

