### **3. To evaluate safety by assessing acute drug toxicity and 30 day surgical morbidity**

The acute drug toxicity and the surgical morbidity will be reported descriptively and the adverse events will be discussed by the DMEC.

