#### 4.4.2 SECONDARY ENDPOINTS

- The pCRM rate will be compared between the control and investigation arms.
- The strength of agreement of the reported mrTRG will be evaluated between the site radiologist versus the central radiologist at site initiation and at the end of the feasibility trial.
- Acute toxicity will be recorded to CTCAE v4.0 protocol. The grade 3- 5 adverse events will be compared between the control and intervention arms on an intention to treat basis.
- Early (30 day) and late (up to 12 months) surgical morbidity will be reported according to the Clavien-Dindo classification
- Quality of surgery will be determined by using the mesorectal grading system and a similar system will be used for grading the quality of APE specimens (Pathology appendix). Outcomes will be compared between the control and intervention arms on an intention to treat basis.

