### 14.2.2 SECONDARY ENDPOINTS

All secondary endpoints will be summarised using descriptive statistics, and will be used to inform the design of the proposed phase III study. The following limited number of endpoints will be summarised by arm, and within arm by patients grouped by mrTRG 1-2 vs. 3-5. Exploratory comparison between arms will be carried out using Fisher's exact test for categorical variables (pCRM rate, proportion with unsalvageable regrowth, proportion of patients with any one or more grade 3-5 toxicity). Quality of surgery and surgical morbidity (maximum Clavien-Dindo grade per patient) will be compared between arms using a Mann-Whitney test. No other formal statistical comparison will be made between arms or mrTRG subgroups for endpoints not listed below.

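### The protocol gives contradictory populations for the grade 3–5 toxicity comparison: whole randomised arms in Section 4.4.2, poor responders only in the lists of Section 14.2.2

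*Protocol*

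**What the plan says.** Four places in the protocol deal with this endpoint.

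- Section 4.2, objective 3: "The acute drug toxicity and the surgical morbidity will be reported descriptively and the adverse events will be discussed by the DMEC". No test and no subgroup is mentioned.
- Section 4.4.2: "The grade 3- 5 adverse events will be compared between the control and intervention arms on an intention to treat basis". No subgroup is mentioned.
- Section 14.2.2, opening paragraph: "Exploratory comparison between arms will be carried out using Fisher's exact test for categorical variables", with the variables given in brackets, among them the "proportion of patients with any one or more grade 3-5 toxicity". On summaries it says: "The following limited number of endpoints will be summarised by arm, and within arm by patients grouped by mrTRG 1-2 vs. 3-5". It closes with a restriction: "No other formal statistical comparison will be made between arms or mrTRG subgroups for endpoints not listed below".
- Section 14.2.2, lists: there are three, for all patients, good responders (mrTRG 1–2) and poor responders (mrTRG 3–5). The toxicity item, "The grade 3- 5 outcomes will be compared between the control and intervention arms on an intention to treat basis", is only in the third. The all-patients list holds pCRM rate, mrTRG agreement, surgical morbidity and quality of surgery.

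On who reads the grade, Section 4.2, objective 1 says of the control arm: "we will report the mrTRG grade in the control arm by centralised assessment". Appendix 6 (image transfer) says that local reports, not the central review, guide management. Section 4.2, objective 2 and Section 14.2.2 also provide for central mrTRG scores on intervention-arm scans.

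**The concern.** One endpoint has two stated populations. Someone working from Section 4.4.2 would run the Fisher test on every randomised patient. Someone working from the lists in Section 14.2.2 would run it on poor responders only, and both could cite the protocol. The trial is open-label, so the choice could be made after data have been seen.

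The narrower choice is the weaker one. Response grade is known only after randomisation, so a poor-responder contrast does not carry the protection of the randomised comparison, whatever label it bears. It also leaves out the intervention-arm good responders. Section 8.2 plans 24 weeks of chemotherapy for them while surgery is deferred, so they are exposed to the toxicity being measured. Safety is a stated aim of the feasibility phase (Section 3.1) and the third secondary objective.

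**Working it through.** The protocol gives no toxicity rate, effect size or significance level for this comparison, so there is no planned figure to reproduce. The check is mainly textual.

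**1. Do the lists in 14.2.2 define populations?** pCRM appears in the all-patients list and again in the good-responder list. Where both a whole-arm and a subgroup comparison were wanted, the endpoint was entered twice. Toxicity is entered once, under poor responders. On that pattern the headings say who is analysed.

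**2. Does the opening paragraph settle the population?** It names grade 3–5 toxicity for the Fisher test with no subgroup limit, which points towards whole arms. But the same bracket names unsalvageable regrowth, which is listed only under good responders and which Section 11.3 defines as arising in tumours first managed by deferral of surgery. Being named there tells us which test applies, not in which patients. The sentence on summaries by arm covers description, not the test.

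**3. Is the poor-responder set an intention-to-treat set?** Section 7.1.2 requires consent to randomisation at least one week before the post-chemoradiotherapy MRI. Section 7.4.1 requires the radiologist to be told the arm so that the right form is used. The grade is therefore assigned after allocation, and selecting on it gives a subgroup, not the randomised population.

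**4. Which reading forms the subgroup?** Control grades are central. Intervention-arm scans have a local grade (used for management) and a central grade (used for the agreement analysis). The toxicity item does not say which applies. If the local grade were used in one arm and the central grade in the other, each site–central disagreement across the 2/3 boundary would reclassify patients in the intervention arm only.

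**5. How many patients are affected?** Inputs: 90 patients (Trial Summary) at 2:1 (Section 3.2), so 60 intervention and 30 control. The share of good responders is my assumption, 30–50%.

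- Intervention: 0.30 × 60 = 18 to 0.50 × 60 = 30 leave the test.
- Control: 0.30 × 30 = 9 to 0.50 × 30 = 15 leave the test.
- Remaining: 42 to 30 intervention and 21 to 15 control.

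**6. What does this do to the test?** As an illustration only, exact power of a two-sided 5% Fisher test by full enumeration. The toxicity rates and the 5% level are assumptions, with the same rates taken in the subgroup as in the whole arms.

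| Assumed rate, control v intervention | All patients (30 v 60) | Poor responders 70% (21 v 42) | Poor responders 50% (15 v 30) |
|---|---|---|---|
| 20% v 40% | 43% | 31% | 21% |
| 20% v 50% | 78% | 61% | 42% |
| 30% v 50% | 41% | 28% | 18% |

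Power is limited in either population. It is clearly lower in the subgroup.

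**The case against.** The strongest reply is that the opening paragraph of 14.2.2 already gives the whole-arm test. It names grade 3–5 toxicity for a between-arm Fisher test, asks for summaries by arm, and its restriction concerns endpoints that are not listed. Toxicity is listed, so the whole-arm comparison is not excluded. Good responders also keep a place in the by-arm summaries and have their own mrTRG 1–2 summary.

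Much of this stands. A reader might infer that 14.2.2 bars the whole-arm comparison, so that it disappears from the plan. The wording does not support that, because the restriction is on unlisted endpoints and not on the populations of a listed one. A reader might also infer that the poor-responder contrast is the only safety comparison tested. It is not: pCRM rate, which Section 4.2 treats as a safety measure, and surgical morbidity are both tested and both stand in the all-patients list.

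Two further points are fair. First, no passage says that the local reading will define the intervention-arm subgroup for analysis. Central scores are planned for both arms, and a SAP not shown here could specify them, so the reader mismatch is a possibility and not a stated rule. Second, Appendix 2 offers the same chemotherapy to the control arm and to both intervention subgroups with different timing, so the 24 weeks are not peculiar to good responders. They are exposed like the others, and that is enough reason not to leave them out.

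The reply does not remove the contradiction. The opening paragraph is silent on population for every variable it names, and the only place in 14.2.2 that does state a population for toxicity is the poor-responder heading. Nor is this a detail left for the SAP: the protocol has already stated the population, in two ways that do not agree.

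**Conclusion.** The point holds as an inconsistency in the stated analysis population. Section 4.4.2 gives whole arms by intention to treat. The lists in 14.2.2 give poor responders only, under an intention-to-treat label that does not fit a subgroup formed after randomisation. The opening paragraph of 14.2.2 is undecided, and Section 4.2 describes reporting without a test. It does not follow that the whole-arm comparison is forbidden or lost, or that toxicity would otherwise be the sole safety test.

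If the lists were followed, 27 to 45 of 90 patients (18 + 9 to 30 + 15) would be outside the test. That range rests entirely on the assumed 30–50% good responders. The nearest figure in the protocol, up to 30% with a complete or near-complete response (Section 1), is a different measure. The power figures rest on assumed rates and show direction only.

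Severity is minor. Section 14.2.2 makes these comparisons exploratory, the trial is a feasibility study, and no toxicity test is stated to decide whether phase III goes ahead.

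**What to change.** In Section 14.2.2, enter grade 3–5 toxicity in the all-patients list as the exploratory intention-to-treat Fisher comparison, so that it agrees with Section 4.4.2. Reword objective 3 in Section 4.2 so that it allows for that exploratory test alongside the descriptive report. Keep the mrTRG 3–5 contrast under its present heading as a subgroup summary, remove the intention-to-treat label there, and state that the central reading defines the subgroup in both arms.

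The cost is one list entry moved and two sentences edited. Central readings are already planned for both arms and toxicity is already collected in every pathway, so no new data are needed.

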## **15. ORGANISATION**

To ensure the smooth running of TRIGGER and to minimise the overall procedural workload, it is proposed that each centre should designate individuals who would be chiefly responsible for local coordination of the surgical and administrative aspects of TRIGGER. The TRIGGER Trial Office will provide as much assistance as they can to local co-ordinators and investigators in obtaining Trust approval in each centre and helping resolve any local problems that may be encountered.

### **15.1 FUNDING**

The TRIGGER feasibility study will be funded by a pump-primed grant from the Pelican Cancer Foundation with agreed adoption to NIHR Clinical Research Network portfolio. This will have benefits in coordination of research efforts, dissemination of trial information and local support for investigators. Inclusion of patients in the TRIGGER trial should incur only minimal additional costs for participating hospitals. Follow-up appointments can be co-ordinated to fit in with the patient's existing follow-up schedule. Funding for the phase III trial will be applied for from the NIHR.

### **IMAGING**

Hospital trusts will not be reimbursed for the staging and restaging MRI(s) or for follow up imaging associated with routine clinical care.

Detailed information about pathways for sending anonymised MRI scans back to the central office for interpretation will be provided on a site by site basis. For hospitals with PACS links, there will be provision for anonymised electronic transfer. For centres without these links, there will be provision for secure postage of a CD back to the TRIGGER Trial Office at the Royal Marsden.

## **15.2 PRINCIPAL INVESTIGATOR AT EACH CENTRE**

Each TRIGGER centre should nominate a Consultant Colorectal Surgeon or Oncologist to act as the local Principal Investigator and bear responsibility for the conduct of research at their centre. The responsibilities of the local Principal Investigator (PI) will be to ensure that all medical and nursing staff involved in the care of potential patients are well informed about the trial and trained in trial procedures, including obtaining informed consent. Close collaboration between all clinical teams is particularly important in order that patients for whom the TRIGGER trial is an option can be identified sufficiently early for entry.

The local PI will also be responsible for ensuring adherence to the protocol. The local PI should liaise with the Trial Manager on logistic and administrative matters connected with the trial.

## **15.3 CENTRAL COORDINATION**

The Trial Office at the Royal Marsden is responsible for providing the following trial materials:

- The Investigator Site File, containing all documentation required to define the involvement of the centre in the trial.
- An Investigators' folder containing printed materials, such as the CRFs, participant information sheets, consent forms and GP letters.
- An Imaging Manual including details relating to scan acquisition and scan transfer.
- A Laboratory Manual

Additional supplies of any printed material can be obtained on request. The Trial Office also provides the central randomisation service and is responsible for collection and checking of data and for reporting of serious adverse events to the sponsor and regulatory authorities on behalf of the Chief Investigator and for any interim and final data analyses. The Trial Office will help resolve any local problems that may be encountered in trial participation.

## **15.4 CLINICAL QUERIES**

During office hours, the relevant member of the trial team (see page iii) may be contacted about clinical queries.

## **15.5 PUBLICATIONS**

A meeting will be held at the end of the trial to allow discussion of the main results among the collaborators prior to publication. The success of the trial depends entirely on the wholehearted collaboration of a large number of doctors, nurses and researchers. Centres will not be permitted to publish data obtained from participants in the TRIGGER trial that uses trial outcome measures without discussion with the Chief Investigator and the Trial Steering Committee.

## **16. RESEARCH GOVERNANCE**

The conduct of the trial will be in accordance with the clinical trials regulations, the principles of Good Clinical Practice and the Declaration of Helsinki.

### **SPONSOR**

National sponsorship will be provided by the Royal Marsden NHS Foundation Trust upon signing of the Clinical Study Site Agreement with each trial site.

### **CLINICAL TRIALS UNIT**

Data from this trial will be handled by the Royal Marsden. This is a full-time research facility dedicated to, and with substantial experience in, the design and conduct of randomised clinical trials. The Royal Marsden recognises the responsibilities of a data management centre with respect to the ethical practice of research and the adequate protection of human subjects.

### **CONFIDENTIALITY OF PERSONAL DATA**

The trial will collect personal data about participants, and medical records will be reviewed for all patients and routine physical examinations will be performed. Participants will be informed that their trial data and information will be securely stored at the trial office at the Royal Marsden, and will be asked to consent to this. The Royal Marsden abides by the UK law Data Protection Act 1998. The data will be stored on a secure computer database, and all personal information obtained for the study will be held securely and treated as strictly confidential. Any data transferred outside of the Royal Marsden will be fully anonymised.

## **LONG-TERM STORAGE OF DATA**

In line with Good Clinical Practice guidelines, all essential documentation and data will be retained for at least 25 years.

## **INDEMNITY**

TRIGGER was developed by the MERCURY III study group and the Royal Marsden, and the feasibility study is being supported by The Pelican Cancer Foundation. The Royal Marsden NHS Foundation Trust is the trial Sponsor. The normal NHS indemnity liability arrangements for clinician initiated research will, therefore, operate. It should be noted, however, that negligent liability remains the responsibility of the hospital, whether or not a patient is part of a clinical trial, because of the duty of care that the hospital has for their patients.

## 17. ABBREVIATIONS AND DEFINITIONS:

|                        |                                                                                                                                                                                                                                                                                                                                                                                                                                                                                                                    |
|------------------------|--------------------------------------------------------------------------------------------------------------------------------------------------------------------------------------------------------------------------------------------------------------------------------------------------------------------------------------------------------------------------------------------------------------------------------------------------------------------------------------------------------------------|
| APE                    | Abdominoperineal excision                                                                                                                                                                                                                                                                                                                                                                                                                                                                                          |
| CEA                    | Carcinoembryonic antigen – a tumour marker for colorectal cancer                                                                                                                                                                                                                                                                                                                                                                                                                                                   |
| COREC                  | Central Office for Research Ethics Committees                                                                                                                                                                                                                                                                                                                                                                                                                                                                      |
| CRM                    | Circumferential Resection Margin                                                                                                                                                                                                                                                                                                                                                                                                                                                                                   |
| CRT                    | Chemoradiotherapy                                                                                                                                                                                                                                                                                                                                                                                                                                                                                                  |
| CTCAE                  | Common Terminology Criteria for Adverse Events - describe the severity of organ toxicity for patients receiving cancer therapy. Toxicity is graded as mild (Grade 1), moderate (Grade 2), severe (Grade 3), or life-threatening (Grade 4), with specific parameters according to the organ system involved. Death (Grade 5) is used for some of the criteria to denote a fatality.                                                                                                                                 |
| EORTC                  | The European Organisation for Research and Treatment of Cancer                                                                                                                                                                                                                                                                                                                                                                                                                                                     |
| FDG-PET                | F  Fluorodeoxyglucose-positron emission tomography – a measure of tissue glucose uptake, this correlates with tissue metabolism in certain types of tissue.                                                                                                                                                                                                                                                                                                                                           |
| GCP                    | Good Clinical Practice - is a quality standard for research that is defined in the clinical trials regulations.                                                                                                                                                                                                                                                                                                                                                                                                    |
| LAR                    | Low Anterior Resection                                                                                                                                                                                                                                                                                                                                                                                                                                                                                             |
| Low Rectal Cancer      | Lower edge of the tumour < 6cm from the anal verge                                                                                                                                                                                                                                                                                                                                                                                                                                                                 |
| MedDRA                 | Medical Dictionary for Regulatory Activities                                                                                                                                                                                                                                                                                                                                                                                                                                                                       |
| MRI                    | Magnetic Resonance Imaging                                                                                                                                                                                                                                                                                                                                                                                                                                                                                         |
| mrTRG                  | Magnetic Resonance Tumour Regression Grade                                                                                                                                                                                                                                                                                                                                                                                                                                                                         |
| NBOCAP                 | National Bowel Cancer Audit Programme                                                                                                                                                                                                                                                                                                                                                                                                                                                                              |
| pCRM involvement       | pCRM – pathological circumferential resection margin. pCRM involvement is defined as tumour ≤ 1mm from the circumferential resection margin at histopathological analysis. For the purpose of the trial, if a patient in the deferral of surgery arm does not undergo an operation and remains 'regrowth' free at 3-year follow-up this will also be defined as pCRM negative.                                                                                                                                     |
| QoL                    | Quality of Life                                                                                                                                                                                                                                                                                                                                                                                                                                                                                                    |
| RCT                    | Randomised Control Trial                                                                                                                                                                                                                                                                                                                                                                                                                                                                                           |
| REC                    | Research Ethics Committee                                                                                                                                                                                                                                                                                                                                                                                                                                                                                          |
| RTOG                   | Radiation Therapy Oncology Group                                                                                                                                                                                                                                                                                                                                                                                                                                                                                   |
| TRIGGER                | Magnetic Resonance Tumour Regression Grade (mrTRG) As A Novel Biomarker To Stratify The Management Of Good And Poor Responders To Chemoradiotherapy: A Rectal Cancer Multicentre Randomised Control Trial                                                                                                                                                                                                                                                                                                          |
| yMRI                   | The post chemoradiotherapy MRI scan. This scan is compared with the baseline MRI in order to perform the mrTRG.                                                                                                                                                                                                                                                                                                                                                                                                    |
| QALY                   | Quality Adjusted Life Years                                                                                                                                                                                                                                                                                                                                                                                                                                                                                        |
| WHO performance status | 
(Grade 0 -5)
 
0 = Able to carry out normal activity without restriction; 1 = Restricted in physical strenuous activity but ambulatory and able to carry out light work; 2 = Ambulatory and capable of self-care but unable to carry out any work; up and about more than 50% of working hours; 3=Capable only of limited self-care; confined to bed or chair ore than 50% of waking hours; 4 = Completely disabled; cannot carry out any self-care; totally confined to bed or chair; 5 = Dead
 |

